## Abstract

**Background:**

Paediatric fractures are highly prevalent and are most often treated with plaster. The removal of plaster is often an anxious experience for children. Virtual reality (VR) has proven to effectively distract children and reduce their anxiety in other clinical settings. This study aims to investigate the effect of VR on the anxiety level of children with fractures that undergo plaster removal or replacement in the plaster room.

**Methods:**

This study is designed as a randomised controlled trial (RCT). The sample size is 270 patients, aged 5 to 17 years, with a fracture of the upper or lower extremity treated with plaster. The intervention group will be distracted with VR goggles and headphones during the replacement or removal of the plaster, whereas the control group will receive standard care. As a primary outcome, the level of anxiety will be measured with the Child Fear Scale (CFS). Secondary outcomes include anxiety reduction (difference between CFS after and CFS before plaster procedure) and Numeric Rating Scales (NRS) pain and satisfaction. Additionally, the children’s fastest heart rate during the procedure will be recorded. An unpaired samples *t*-test or a Mann-Whitney *U* test (depending on the data distribution) will be used to analyse the data.

**Discussion:**

When completed, this trial will provide evidence on the potential role of VR in children with fractures treated with plaster. The purpose is to increase the quality of healthcare by decreasing anxiety and possibly pain perception of children during a plaster procedure.

**Trial registration:**

Netherlands Trial Register NL9065. Registered on 27 November 2020

## Administrative information

Note: The numbers in curly brackets in this protocol refer to SPIRIT checklist item numbers. The order of the items has been modified to group similar items (see https://clicktime.symantec.com/3S6ewNUXrUE2dhpUYYBaKws6Gu?u=http%3A%2F%2Fwww.equator-network.org%2Freporting-guidelines%2Fspirit-2727-statement-defining-standard-protocol-items-for-clinical-trials%2F).

## Introduction

### Background and rationale {6a}

Fractures occur frequently in children; the prevalence of paediatric fractures in The Netherlands is 40% for males and 28% for females between the ages of 6 and 16 [1]. The far majority of these children receive plaster treatment. The removal of plaster is often an anxious experience for children, particularly under the age of 13 [2, 3]. Methods to effectively reduce this anxiety may improve their hospital experience.

Different methods have been investigated to reduce anxiety in children in various clinical situations. Many of these methods have proven to be ineffective, such as using midazolam [4] and showing an instructional video ahead of the procedure [5]. However, a few methods were found that reduced the anxiety: watching videos on a smartphone or tablet during the procedure [6, 7] and using noise-reducing headphones during plaster removal [2]. Virtual reality (VR) has proven to reduce anxiety and pain perception of children in other clinical situations, such as blood draws, dental procedures, intravenous injections and treatment of burns [8–12]. The use of VR may be more effective in reducing anxiety and pain perception than a tablet [7]. A pilot study on VR in the plaster room has shown promising results [13].

Therefore, the aim of this study is to further investigate the anxiety-reducing effects of VR in a large group of children with fractures who undergo plaster replacement or removal. Our hypothesis is that the use of VR will reduce the anxiety of children with fractures in the plaster room and increase their satisfaction. We also hypothesise that younger children will benefit more than older children, based on experience with ear protection [3].

### Objectives {7}

The primary objective of this study is to evaluate the difference in the post-procedural anxiety level in children in the plaster room with or without distraction with use of VR. The secondary objectives of this study include anxiety reduction (difference between CFS scores pre- and post-procedural), level of pain experienced (using the numeric rating scale (NRS)), satisfaction scores (NRS) given by the child and the accompanying parent/guardian and the child’s fastest heart rate measured by a finger pulse oximeter during the procedure.

### Trial design {8}

The study is designed as a randomised controlled monocenter superiority trial with two parallel groups, with the children’s anxiety as the primary outcome. The randomisation will be stratified for age with a 1:1 allocation.

## Methods: participants, interventions and outcomes

### Study setting {9}

This study will be performed in the plaster room of the Amphia Hospital in Breda, The Netherlands.

### Eligibility criteria {10}

Patients and/or both legal guardians (depending on the child’s age) must provide written, informed consent before any study procedures occur (see Appendix 1–6 for the various informed consent forms).

#### Inclusion criteria

In order to be eligible to participate in this study, a subject must meet all of the following criteria:Age 5–17 years.At least one fractured bone in the upper or lower extremity.Needs replacement or removal of plaster.Children can only participate once in this study.

#### Exclusion criteria

A potential subject who meets any of the following criteria will be excluded from participation in this study:Children who have already participated in this study at a previous plaster treatmentChildren with known mental retardation, anxiety disorder, psychosis or epilepsyChildren with an extreme visual impairment (i.e. myopia > 8 dioptres or presbyopia > 5 dioptres)Children and parents with an insufficient understanding of the Dutch or English language to give informed consent

### Who will take informed consent? {26a}

The informed consent will be obtained by the researcher. The children and parents will first be informed by posters and flyers in the emergency room. Subsequently, the parents/guardians and the patients themselves will be informed by telephone about the project, about their right to withdraw at any time, and the instructions for signing the informed consent. If they are interested to participate, the children and parents are sent the written patient information and informed consent in duplicate, with the request to bring signed copies. If the child is under 16, both parents and guardians must sign the consent form prior to inclusion.

In the plaster room of the Amphia Hospital in Breda, the patient and accompanying parent/guardian receive verbal information about the study again, and the informed consent forms are handed in and signed by the researcher. One copy of the informed consent forms is returned to the patient and parent/guardian.

### Additional consent provisions for collection and use of participant data and biological specimens {26b}

Not applicable.

### Interventions

#### Explanation for the choice of comparators {6b}

In this study, the control group will receive standard care with the addition of a finger pulse oximeter (Onyx Vantage 9590, manufactured by Nonin Medical, Inc., in Plymouth, MN, USA). The intervention group will receive standard care with the addition of a finger pulse oximeter, VR goggles (Oculus Go or Oculus Quest 2, manufactured by Facebook Technologies, LLC in Menlo Park, CA, USA) and headphones (JBL JR300 Junior, manufactured by HARMAN International in Stamford, CT, USA). Standard care consists of the orthopaedic practitioner explaining the procedure and then removing or replacing the plaster. Standard care is chosen as the control, because the purpose is to investigate whether the addition of VR will decrease the anxiety level and thereby improve the patient’s experience during the plaster treatment.

#### Intervention description {11a}

The investigational group will receive standard care and will wear the VR goggles and headphones as well as a finger pulse oximeter during the plaster procedure. The VR goggles will play a video during the procedure to distract the child. The headphones will make sure that the child is more focused on the video by playing the sound of the video and by drowning out the noise of the procedure.

The control group will receive standard care and will wear the finger pulse oximeter.

Each age group (5–11 and 12–17) will have a choice between two videos of approximately 20 min long. The video length is based on the maximum length of the plaster intervention. The children can choose between single episodes of different series on Netflix. The content of the video is based on Netflix recommendations and is screened to make sure the content is appropriate for the hospital setting and the age group.

Children between the ages of 5 and 11 years have a choice between Masha and the Bear season 1 episode 2 and The Thundermans season 1 episode 2; children aged 12–17 years can choose between Modern Family season 1 episode 2 and Brooklyn Nine-Nine season 1 episode 2.

Masha and the Bear is an animated series that focusses on the adventures of a little girl named Masha and a fatherly bear that keeps her safe and prevents disasters. The Thundermans is a comedy series that revolves around the Thundermans, a family with superpowers who try to live normal lives. The spoken language of both videos is set to Dutch.

Modern Family is a sitcom and follows the lives of three diverse families and is filmed from the perspective of an unseen documentary maker. Brooklyn Nine-Nine is a comedy series following the immature but talented NYPD detective Jake Peralta and his diverse, lovable colleagues as they police the NYPD’s 99th precinct. The spoken language of both videos is set to English with Dutch subtitles.

Before the procedure, the child’s anxiety and pain scores are collected with a short questionnaire, using the Child Fear Scale (CFS) [14] and the Numeric Rating Scale (NRS pain), respectively. Then, the orthopaedic practitioner explains the plaster procedure, the finger pulse oximeter is put on and the randomisation result is revealed.

If the child is assigned to the control group, the plaster procedure is then performed by the orthopaedic practitioner. If the child is assigned to the intervention group, the investigator starts the video of choice and places the VR goggles and headphones on the child’s head (adjusting the straps if necessary) before the plaster procedure is performed by the orthopaedic practitioner. During the plaster treatment, the child’s fastest heart rate is recorded by the investigator, using the finger pulse oximeter.

After the procedure, the VR goggles, headphones and finger pulse oximeter are removed. Hereafter, the child’s anxiety and pain scores are collected once more using the CFS^15^ and NRS pain. Additionally, the child and accompanying parent/guardian are asked to rate their satisfaction with the procedure, using the NRS satisfaction.

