### Outcomes {12}

The main study outcome parameter is the difference in post-procedural anxiety scores in the intervention and control groups, using the Child Fear Scale (CFS) [15]. The secondary study parameters are the differences between the two groups in anxiety reduction (difference between the child’s CFS score pre- and post-procedural), NRS pain given by the child (pre- and post-procedure), NRS Satisfaction Score given by the child and accompanying parent/guardian and the child’s fastest heart rate measured by a finger pulse oximeter during the procedure.

The following demographic data is collected from the patient’s medical records: date of fracture, date of plaster intervention, age, sex, upper or lower extremity fracture, specific location of the fracture, type of plaster treatment (plaster replacement or removal) and previous experiences with plaster removal. After randomisation, additional demographic data is collected from the patient or accompanying parent/guardian and the orthopaedic practitioner before the plaster intervention (e.g. the use of pain killers, method of plaster removal, and the video chosen (if assigned to the intervention group)).

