### Participant timeline {13}

In the emergency room, the patient and parent/guardian are first informed about the study through posters and the informational flyer provided by the attending physician (Fig. 1). The patients and parents/guardians will be further informed about the study by the investigator by phone a few days prior to the scheduled appointment in the plaster room. If they are interested in participating, they will be sent written patient information and consent forms. In the plaster room, the investigator will collect the signed consent forms. The patients are then enrolled in the study and will complete a short questionnaire. Afterwards, the patient will be randomised, and the equipment (finger pulse oximeter, VR goggles and headphones) is placed on the child. The patient will then receive the plaster treatment. Right after the plaster intervention, all the equipment is removed. Lastly, a short questionnaire will be conducted with the child and parent. This concludes the participation of the child in this study.

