### Data collection and management

#### Plans for assessment and collection of outcomes {18a}

The following demographics of the patient are collected from the patient’s medical records: date of fracture, date of plaster intervention, age, sex, upper or lower extremity fracture, specific location of the fracture, type of plaster treatment (plaster replacement or removal) and previous experiences with plaster removal. After randomisation, additional demographic data is collected from the patient or accompanying parent/guardian and the orthopaedic practitioner before the plaster intervention (e.g. the use of pain killers, method of plaster removal (if applicable) and the video chosen (if assigned to the intervention group)).

Additionally, data is collected with short questionnaires before and after the procedure. The child’s anxiety and pain scores are collected before and after the procedure, using the Child Fear Scale [15] (CFS) and the Numeric Rating Scale (NRS pain), respectively. The child’s and parent’s satisfaction will be collected after the procedure using the NRS satisfaction.

Lastly, the child’s fastest heart rate (during the procedure) is collected with the finger pulse oximeter.

All data is collected by a single individual. The principal investigator will randomly check the data entry during the study.

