## Statistical methods

### Statistical methods for primary and secondary outcomes {20a}

The outcomes of both groups will be compared with the use of an independent samples *t*-test or a Mann-Whitney *U* test, depending on the distribution of the data, assessed using a histogram and an independent samples Kolmogorov-Smirnov (K-S test). If the data is normally distributed, an independent *t*-test will be performed, and the mean and standard deviation will be reported. If the data is not normally distributed, a Mann-Whitney *U* test will be performed, and the median and (interquartile) range will be reported.

The statistical package SPSS (version 25, IBM Corp, Armonk, NY, USA) will be used for all statistical analyses. *P*-values < 0.05 are considered significant for the primary outcome. The significance level of the secondary outcomes will be adjusted to multiple testing according to the Holm method [14].

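### Fastest heart rate is compared without adjusting for age or for a pre-allocation reading; the comparison stays unbiased but may lose precision that is cheap to recover

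*Protocol article*

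**What the plan says.** **What is measured.** Outcomes {12} lists as a secondary outcome the child's "fastest heart rate measured by a finger pulse oximeter during the procedure". Intervention description {11a} says "During the plaster treatment, the child’s fastest heart rate is recorded by the investigator, using the finger pulse oximeter", and the data-collection section {18a} repeats it: "Lastly, the child’s fastest heart rate (during the procedure) is collected with the finger pulse oximeter". These sections agree on a single value per child. The measurements named for the time before the procedure are the fear and pain scores: "Before the procedure, the child’s anxiety and pain scores are collected with a short questionnaire". No resting or pre-procedure heart rate is listed.

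**When the oximeter goes on.** Intervention description {11a} places it after the questionnaire and the explanation: "the finger pulse oximeter is put on and the randomisation result is revealed". Participant timeline {13} words the sequence differently: "Afterwards, the patient will be randomised, and the equipment (finger pulse oximeter, VR goggles and headphones) is placed on the child".

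**How it is analysed.** Statistical methods {20a} applies one rule to all outcomes: "The outcomes of both groups will be compared with the use of an independent samples *t*-test or a Mann-Whitney *U* test", chosen by the shape of the data. No covariate is named. Sequence generation {16a} stratifies randomisation by age (5–11 and 12–17), on the ground that age may influence the outcomes. Additional analyses {20b} plans age subgroups, but this does not adjust the main comparison.

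**The concern.** No one is blinded {17a}, and fear, pain and satisfaction are ratings by children or parents who know the allocation. Heart rate is the one outcome that is not a rating, and the article's Discussion names it beside the Child Fear Scale as this study's way of measuring anxiety. It is worth measuring as sharply as the set-up allows.

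Differences between children in their usual heart rate, whether from age or from their state on arrival, are noise in the comparison of arms. Part of that noise could be removed with age, which is already collected. A further part could be removed with a reading on the same device before the child learns the allocation. The plan does neither, whereas fear and pain each have a pre-procedure value.

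At stake is the width of the confidence interval for this outcome, and so how much a null heart-rate result would mean. An analysis plan written later could add age. It could not adjust for a baseline that was never collected.

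**Working it through.** **1. The plan's own figure.** The only sample-size calculation {14} concerns the Child Fear Scale: difference 0.5, SD 1.40, power 80%, alpha 0.05 (two-sided assumed). The normal formula gives 2 × [(1.960 + 0.842) × 1.40 / 0.5]² = 123.1 per group, and the t-based calculation gives 124.0, against 123 stated. The figure reproduces. It says nothing about heart rate, for which the document gives no SD, correlation or target difference.

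**2. Inputs for heart rate.**
- Evaluable children per group: 135 × 0.9 = 121.5, taken as 121 (from {14} and the 10% loss in {20c}).
- Correlation r between the pre-reveal and the fastest rate: assumed, 0.3 to 0.7.
- True difference: assumed, 0.3 SD of fastest heart rate.
- First Holm step: 0.05 / 5 = 0.01, assuming five secondary tests (anxiety reduction, pain, child satisfaction, parent satisfaction, heart rate).

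**3. Formulas.** With a baseline for every child, ANCOVA leaves a share 1 − r² of the variance. The standardised effect becomes 0.3 / √(1 − r²), and power follows from the two-sample t-test with 121 per group.

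| r | Variance left | Removed | Effect (SD) | Power at 0.05 | Power at 0.01 |
|---|---|---|---|---|---|
| 0 (raw) | 1.00 | 0% | 0.300 | 64% | 40% |
| 0.3 | 0.91 | 9% | 0.314 | 68% | 44% |
| 0.4 | 0.84 | 16% | 0.327 | 72% | 48% |
| 0.5 | 0.75 | 25% | 0.346 | 77% | 54% |
| 0.7 | 0.51 | 49% | 0.420 | 90% | 75% |

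**4. Children already enrolled.** Trial status gives a start of 21 January 2021 and an anticipated end of 1 April 2022, but no enrolment count. If a share f of children has no baseline and receives the mean, the variance left is about 1 − (1 − f)r². With f = 0.5:
- r = 0.5: 1 − 0.5 × 0.25 = 0.875; power 70% at 0.05 and 46% at 0.01.
- r = 0.7: 1 − 0.5 × 0.49 = 0.755; power 76% at 0.05 and 54% at 0.01.

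With f = 0.75, power at 0.05 is 67% (r = 0.5) to 70% (r = 0.7).

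**5. Why a covariate and not a change score.** With equal variances, the variance of the change is 2(1 − r) times the raw variance: 1.4 at r = 0.3, 1.0 at r = 0.5 and 0.6 at r = 0.7. Subtracting the baseline would lose precision whenever r is below 0.5. ANCOVA does not have this problem.

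**6. The two sequences.** {11a} speaks of when the result is revealed; {13} speaks of when the child is randomised and when all the equipment is placed. Both are satisfied if the system allocates the child, the oximeter goes on, the result is revealed, and the goggles follow. Read literally, though, {13} would let the oximeter go on after the allocation is known.

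**The case against.** The strongest case against is that nothing here is an error. The outcome is defined consistently, the arms are randomised within age strata, and the raw comparison is unbiased. It is one of several secondary outcomes, and the primary conclusion does not depend on it. On this view, adding a measurement and a covariate is a matter of taste. The validity part stands in full. The taste part does not: the protocol stratifies on age because age may matter and then ignores it in the test. Where age is prognostic, this gives up precision and makes the test slightly conservative. No drawback beyond a small data-collection cost has been shown.

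A reader might infer that the heart-rate comparison loses much of its precision. The document does not support that. It gives no correlation, and at 0.3 to 0.4 only 9% to 16% of the variance would be saved. The larger gains also require a baseline from every child, which a trial already recruiting cannot have.

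A reader might also infer that {11a} and {13} flatly contradict each other. They can be read together, so this is a matter of wording to reconcile.

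Nor should heart rate be treated as immune to bias. An unblinded investigator records it and one individual collects all data, and a baseline reading would not cure that.

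**Conclusion.** The point holds as a modest, optional improvement. Fastest heart rate is analysed without age, although age is collected and stratified on, and without a baseline that the {11a} sequence would allow. The effect is a possible loss of efficiency in one secondary outcome, with no bias and no consequence for the primary analysis.

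The size depends on an assumed correlation: slight at 0.3 and substantial from about 0.5. The power figures rest further on an assumed 0.3 SD effect and, at 0.01, on an assumed count of five secondary tests. The gain that can be realised shrinks with the share of children already enrolled, which the document does not give. Age adjustment alone would recover part of the gain for everyone; how much cannot be computed from the document.

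**What to change.** 1. In {20a}, name a linear model (ANCOVA) for fastest heart rate with arm and age in years as terms, for all children, in place of the choice between two unadjusted tests. Age is already collected, so this costs one line of text.
2. Reconcile {11a} and {13} so that both state that the oximeter is on before the allocation is revealed.
3. For children still to be enrolled, record one heart rate in a fixed way after the oximeter is on and before the reveal (for example, the highest value over one minute), and add it to the model as a covariate.
4. For children without that reading, impute the overall mean across both arms. This is sound for a covariate measured before randomisation is revealed. State it as an exception to the complete case rule in {20c}, so that no child with a fastest heart rate is dropped for lack of a baseline.

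The cost of steps 2 to 4 is one case report form field, about a minute per child and a short amendment. The benefit of the baseline is limited to children not yet enrolled; if few remain, steps 1 and 2 are still worth making.
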